### Data entry and analysis

All data collection forms will be reviewed by the field supervisors for accuracy and completeness and then transferred to the data entry clerks for double data entry in the field office. The database program will incorporate range and consistency checks. Data will be transferred weekly to IRSS,B (the main coordination office of the study) and will be backed up by internet upload (via a secure connection) to a protected folder on the UC Davis Smartsite. Programs will be developed to detect any outlier data. All data collected by each field worker also will be checked for mean values and number preference, and any retraining will be scheduled, if necessary. The field workers will meet with the field supervisors weekly to discuss any problems that may arise.

Analysis will be on an intention-to-treat basis. Thus, once enrolled, all subjects will be included in the analysis until the time they complete the study, drop out voluntarily, or are withdrawn, for pre-defined reasons. Withdrawn or discontinuing participants are not replaced by others; i.e. possible drop-outs do not influence the sample size, once the study has started. If caregivers refuse blood drawing, other data will still be included in the analysis.

Statistical analysis will be completed with SAS for Windows. The distribution of each outcome variable will be examined, and variables will be transformed as needed to meet the assumptions of normality of residuals and homogeneity of variance. If no suitable transformation can be found, non-parametric techniques will be used. Baseline characteristics of intervention groups will be compared to determine whether any variables differ among groups despite randomization. In addition, baseline characteristics of subjects who are lost to follow-up will be compared with those of subjects who complete the study to assess potential bias due to attrition.

For the primary outcomes of change in length-for-age Z-score, incidence of diarrhea and malaria and change in plasma zinc concentration between 9 and 18 months, the analysis will compare the difference (95% confidence intervals) between means of the control and intervention groups (LNS-Zn5, LNS-Zn10, Suppl-Zn5 versus LNS-Zn0 and all intervention groups versus the delayed intervention control group) using analysis of covariance, controlling for any baseline variables that either differ between groups or are predictive of the outcome.

A test for interaction and stratified analyses will be done to explore whether the effects of zinc on the primary or secondary outcomes are modified by certain baseline characteristics. Variables in this analysis will include the participant's initial length, weight, sex, plasma zinc concentration, erythrocyte zinc protoporphyrin concentration, maternal education, number of siblings, as well as the household food security and income indicators.

Proportion of child deaths before age 18 months and proportion of child drop-out before age 18 months will be compared across the four intervention groups by Fisher's exact test.

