## **PURPOSE AND PROCEDURES:**

This is a multi-center community-based, partially double-blind, placebo-controlled randomized intervention trial. The trial will be a collaborative effort between the Institute of Research in Health Sciences, Burkina Faso (Institut de Recherche en Sciences de la Santé – IRSS,B) and the University of California, Davis, both of which are part of the International Lipid-based Nutrient Supplement (iLiNS) study group, which involves researchers from Burkina Faso, Malawi, Ghana, Finland, France, and the United States. The study is investigator initiated. Funding is provided by a grant from the Bill and Melinda Gates Foundation.

The study uses a cluster sampling design, which consists of 34 communities in the Dandé Health District. Communities will be randomly assigned to either intervention or delayed intervention groups (25 communities in the intervention group, 9 in the delayed intervention group). Within the intervention communities, participants will then be randomized at the level of concession (i.e., the extended family compound) to one of 4 intervention groups as described in more detail below. The total sample size is 3250 children.

**Specific aim:** The specific aim of the study is to assess zinc-related biochemical and functional responses among young Burkinabe children with a presumed high risk of zinc deficiency who receive micronutrient products (lipid-based nutrient supplements (LNS) or zinc supplements) containing different amounts of zinc, provided with or between meals.

The study has 3 **main objectives**:

- 1) To determine the lowest daily dose of zinc in LNS that will promote linear growth among 9- to 18-month-old infants in rural communities in Burkina Faso with high rates of stunting.
- 2) To determine the impact of different zinc doses in LNS on morbidity, micronutrient status, and neuro-behavioral development.
- 3) To examine the extent to which household food insecurity and other individual, household, and village-level characteristics modify the effects of LNS on child outcomes.

The specific **hypotheses** for the trial are as follows:

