### **Anthropometry**

The weight, length, right mid-upper arm circumference, and head circumference of all participants will be measured at baseline in children in both the intervention and non-intervention communities. The weight and length information will allow calculation of the prevalence of stunting (low height-for-age), underweight (low weight-for-age), and wasting (low weight-for-height). Mid-upper arm circumference is a useful parameter for analyzing nutritional status in children aged 6-59 months because it measures muscle mass and can be used as a proxy for wasting. Head size, in part, measures brain growth. Maternal height and weight will also be measured at baseline in both the intervention and non-intervention communities; we will adjust for maternal anthropometric measures in analyses of child growth.

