### Biological sample (blood) collection and laboratory analysis

Micronutrient status of the study population will be assessed by measurement of biochemical markers in blood. Hemoglobin and zinc protoporphyrin concentration will be measured in a drop of capillary blood in all children. Zinc, retinol, retinol-binding protein, plasma ferritin, transferrin receptor, C-reactive protein, and alpha-1 acid glycoprotein concentrations will be measured in plasma processed from venous blood samples in a randomly chosen sub-sample of children in each study group (total sample size of biochemical sub-group: n=626). In the same sub-sample, a few drops of whole blood will be stored on filter paper to assess thyroid hormone status and thyroglobulin concentration.

Anemia will be assessed by measuring hemoglobin in all children. A drop of capillary blood will be obtained by finger stick from each child for hemoglobin assessment using a portable Hemocue photometer (Hemocue, Inc; Lake Forest, CA). Children with hemoglobin <50 g/L will be excluded from the study and referred for further evaluation and treatment. Children with moderate anemia (hemoglobin 50 – 79 g/L) will be treated according the national policy. Namely, they will receive iron supplementation (3-6 mg iron/kg/d for at least 30 days) and an anthelmintic treatment (Mebendazole). These latter participants will remain in the study during and after the additional iron and anthelmintic treatment, and will continue to receive LNS and zinc/placebo supplements, but will be specifically identified in the analyses.

Zinc status of children will be assessed by measuring plasma zinc concentrations by atomic absorption spectrometry (Shimadzu AA-6300; Tokyo, Japan). Vitamin A status of children will be assessed by measuring retinol-binding protein and by measuring plasma retinol determined by reverse-phase high performance liquid chromatography. Iron deficiency will be assessed by measuring erythrocyte zinc protoporphyrin in unwashed and washed red blood cells using a hematofluorometer (Aviv Biomedical, Lakewood, NJ, USA) and by measuring plasma ferritin and transferrin receptor. Iodine and thyroid status indicators (thyroxin, thyroid-stimulating hormone and thyroglobulin concentrations) will be assessed in dried blood spots on filter paper by two-site dissociation enhanced lanthanide fluorescent immunoassay (Delfia) (Perkin Elmer Life Sciences, Wallac, Turku, Finland).

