### Recruitment and enrollment

Individual communities will be stratified by selected indicators (size; proximity to road and the city of Bobo-Dioulasso; and health clinic affiliation) and then randomly assigned within strata to have children participate in the intervention from 9-18 months (~75% of communities) or from 18-27 months (~25% of communities).

Nine-month-old healthy infants will be identified by the periodic censuses in the study area. Children aged 9 months of age whose caretakers show a preliminary interest in the trial will be invited to an information session for further description of the trial design and requirements.

Written, informed consent will be obtained from all study families by study supervisors, using culturally appropriate explanations of all study procedures, benefits, and risks. Separate consent forms will be used for participants in intervention communities and the delayed intervention communities to better describe the respective interventions. An additional consent form will be administered in the biochemical sub-group to obtain written consent for any future analyses in the collected biochemical samples.

Children whose parents sign the consent will undergo a preliminary screening (described below) to determine if they meet the enrollment criteria. Those children meeting all enrollment criteria will be given a trial identification number. Children in the communities that participate in the intervention will be randomly assigned at the level of the concession (i.e., the extended family compound) to one of the four intervention groups.

The age of the participants will be confirmed from eligible subjects' road-to-health under-five cards, which provide the date of birth. Identity cards of each participant will be produced to facilitate identification of the participants.

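### The primary ANCOVA picks its covariates by observed baseline difference or outcome prediction, so the adjusted estimate depends on chance; the covariates should be named in advance

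*Protocol*

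**What the plan says.** The protocol's Data entry and analysis section first announces that "Baseline characteristics of intervention groups will be compared to determine whether any variables differ among groups despite randomization". It then gives the primary outcomes: change in length-for-age Z-score (LAZ), incidence of diarrhea and malaria, and change in plasma zinc. For these, group means are compared with "95% confidence intervals" by analysis of covariance, controlling for "any baseline variables that either differ between groups or are predictive of the outcome". The one rule serves both sets of contrasts: the three zinc arms against LNS-Zn0, and all LNS arms against the delayed-intervention group.

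Four other statements bear on it:

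- **Anthropometry:** "we will adjust for maternal anthropometric measures in analyses of child growth". No condition is attached.
- **Biological sample (blood) collection:** plasma zinc and the other venous markers are measured "in a randomly chosen sub-sample of children in each study group (total sample size of biochemical sub-group: n=626").
- **Purpose and procedures:** allocation has two levels. Communities are allocated first, "25 communities in the intervention group, 9 in the delayed intervention group". Then, "Within the intervention communities, participants will then be randomized at the level of concession".
- **Recruitment and enrollment:** "Individual communities will be stratified by selected indicators", namely size, proximity to road and city, and health clinic affiliation.

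The text at hand gives no candidate list, test or threshold for either limb of the covariate rule. Those details could sit in a statistical analysis plan (SAP). The principle of selection is already fixed here.

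**The concern.** A baseline variable can qualify in two ways. Prognostic value is a sound reason to adjust, although it is better settled in advance. An observed difference between randomised groups is not a sound reason. Such a difference is chance by construction, and it says nothing about whether adjustment will sharpen the estimate.

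The rule is also run separately for each outcome and each contrast. Two analysts who follow it faithfully, with different candidate lists or tests, would report different primary estimates. The difference limb is most easily triggered in the delayed-intervention contrast. Only 34 communities were randomised there, and children in one community tend to resemble each other.

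**Working it through.** **Inputs from the protocol.** There are four LNS groups of about 610 children and about 810 in the delayed group: 4 × 610 + 810 = 3250, which reproduces the stated total. There are 25 + 9 = 34 communities, with average sizes 2440/25 = 97.6 and 810/9 = 90. The interaction paragraph lists nine baseline characteristics: length, weight, sex, plasma zinc, zinc protoporphyrin, maternal education, number of siblings, food security and income indicators. They serve here as a stand-in for a candidate list, because the covariate rule has none.

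**Assumptions.** The baseline check uses a two-sided 5% level, the variables are independent, and the ICC is 0.01 to 0.05. None of these is stated.

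**1. Chance flags with a valid test.** P(at least one of nine) = 1 − 0.95⁹ = 0.37. Correlated variables, such as length and weight, would lower this somewhat. A longer list would raise it.

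**2. Community contrast with a child-level test.** The design effect in each group is 1 + (m − 1) × ICC. The ratio of true to naive variance is

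(DE₁/2440 + DE₂/810) / (1/2440 + 1/810),

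and the false-flag rate per variable is 2 × [1 − Φ(1.96/√ratio)].

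| ICC | DE₁ | DE₂ | Variance ratio | Flag rate, formula | Flag rate, simulation |
|---|---|---|---|---|---|
| 0.01 | 1.97 | 1.89 | 1.91 | 16% | 17% |
| 0.02 | 2.93 | 2.78 | 2.82 | 24% | 25% |
| 0.05 | 5.83 | 5.45 | 5.54 | 41% | 40% |

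The simulation used 4000 runs per ICC with 25 communities of 98 children and 9 of 90. A test on community means flagged 5% to 6% throughout. The excess therefore comes from testing at child level, which the protocol neither states nor rules out. The rates apply to variables measured in all children, so not to plasma zinc.

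**3. Would baseline LAZ be missed?** With equal SDs at 9 and 18 months and correlation r between them, baseline correlates with change at −√((1 − r)/2). For assumed r of 0.91 to 0.73 this is −0.21 to −0.37. With 2 × 610 = 1220 children in one zinc contrast, the smaller value gives z of about 0.21 × √1220 = 7.4. The prediction limb would select baseline LAZ in practice every time.

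**4. Why the list must stay short for the community contrast.** If it is analysed on 34 community values, k irrelevant covariates multiply the expected variance of the group effect by about (34 − 3)/(34 − 3 − k). Relative to three covariates, the SE rises by √(28/24) = 1.08 with seven and √(28/23) = 1.10 with eight.

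**5. The subgroup boundary.** If a marker held only for the 626 entered a growth model fitted on complete cases, 626/3250 = 19% of children would remain. Pro rata that is 610 × 626/3250 = 117 to 118 per arm. Standard errors would grow by √(3250/626) = 2.28.

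**The case against.** Adjustment for prognostic baseline variables is accepted practice. The candidate list, threshold and handling of clustering are ordinary SAP content. The Frequency of analyses section keeps arm identity coded until the main outcomes are analysed, which limits steering among the four LNS arms. All of that stands. It does less for the delayed group, which is recognisable because it has no 12- and 15-month anthropometry. It also does not rescue the difference limb, which an SAP following the protocol would inherit.

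Three stronger readings are tempting, and the document does not support them.

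- **The growth analysis will shrink to 626 children.** This needs a subgroup-only marker to be selected and a complete-case fit, and neither is stated. No passage says that the trial expects plasma zinc to predict growth; it is listed only as a possible effect modifier. Data entry and analysis also promises intention-to-treat analysis of all enrolled children, and keeps the other data of children whose caregivers refuse blood drawing. The loss of about 80% of the sample is a possible literal consequence, not a plan.
- **The Anthropometry section contradicts the rule.** Its maternal measures can be read as a minimum to which the rule adds. The text should say so, but both statements can be met.
- **The outcome's own baseline may be left out.** Step 3 shows that baseline LAZ would pass. It should be named for clarity; no precision is at risk.

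**Conclusion.** The point holds as a defect in a stated method. Selection by observed baseline difference makes the covariate set, and so the adjusted primary estimate, depend on chance. It also lets the set vary between outcomes and contrasts.

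The chance of at least one spurious flag is about 37% under the assumptions of step 1. In the delayed-intervention contrast the per-variable rate rises to about 16% to 41% if differences are tested at child level and the ICC lies between 0.01 and 0.05. With a community-level check it stays at 5% to 6%.

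A reader might infer inflated false positives. That is not claimed: in simulation, Type I error under such selection stayed near 5%. The loss is reproducibility and some precision. How much precision cannot be fixed from the protocol, since it depends on an unstated candidate list, test and level of analysis. The change is worth making because it costs almost nothing.

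**What to change.** Delete selection by baseline difference and name the covariates in the protocol or SAP before children are assigned to groups for analysis:

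- **Growth:** baseline LAZ, age at enrolment, sex, and maternal height and weight, as the Anthropometry section promises.
- **Change in plasma zinc:** its own baseline value.
- **Diarrhea and malaria incidence:** a fixed set of variables measured in all children. There is no ready baseline value of an incidence, so the set must be written out.
- **LNS arms against the delayed group:** add the community stratification indicators from Recruitment and enrollment, coded with few terms because there are only 34 communities.

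As a safeguard, state that markers measured only in the 626-child subgroup are not covariates for whole-sample outcomes. Label any further adjustment as sensitivity analysis.

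The cost is a few lines of wording. The main covariates and the stratification indicators are already part of the planned data. The small downside is that a chance imbalance in an unlisted variable is addressed only in the sensitivity analysis.

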### Frequency of analyses

The main statistical analysis will be done after the last participant attains the age of 18 months and the main intervention is completed. First the dataset will be checked for outliers. Then participants will be assigned to their respective treatment group to allow group-wise analysis. The randomization code revealing the identity of the assigned group will be broken only after the statistical analysis of the main outcomes is completed and only after consulting among all investigators. A further analysis will be done at the end of the follow-up, i.e., when all children reach 42 months of age.

### Nature, frequency and duration of tests

In all children, capillary blood samples will be obtained by finger stick upon enrollment (9 months of age) and at 18 months of age to measure hemoglobin and malaria parasites count. At 9 months, the finger stick will also be used to assess ZPP and malaria antigen. In the biochemistry subgroup, capillary ZPP will also be done at 18 months.

Biochemical indicators of micronutrient status will be assessed in a randomly selected sub-set of children (n=626). For these subjects, caregivers will bring their children to the clinic for the baseline and final specimen collections. Venous blood samples (5 ml whole blood) will be obtained from subjects at the baseline and final clinic visits. The samples will be drawn in the morning at the local community health center. When the child is ill or has had diarrhea or fever during the past two days of a scheduled baseline collection of blood, urine and saliva, the sample collection will be postponed until

the symptoms resolve. Final collection of blood, urine, and saliva will be postponed if the child has a fever  $>38.5^{\circ}\text{C}$  or is acutely ill. In the case of the final biochemical sample, supplementation will be continued until the sample is obtained.

In the intervention groups, the length, weight, right mid-upper arm circumference and head circumference will be measured for all children at the baseline, 12, 15 and 18 months of age during the intervention. The same anthropometric measurements will be completed for children in the delayed intervention group at baseline and 18 months of age. We anticipate that clinic visits including blood sample collection and anthropometry will take approximately 4-5 hours to complete.

In the “biochemistry” subset of children, body composition will be assessed twice, at baseline and 18 months of age, at the health center. We anticipate that the body composition assessment will take approximately 4-5 hours.

Comprehensive tests of development will be performed once at 18 months of age in a randomly selected subgroup of children (600 children from the delayed intervention group and 1350 children from the intervention group [450 children for each of the groups LNS-Zn0, LNS-Zn10, and Suppl-Zn5]). Motor, social, and language development will be assessed every 4 weeks through selected questions from the Denver Development Screening Test 2 during home visits. We anticipate that the tests of development administered in the homes will take approximately 15 minutes to complete. In addition, at baseline, 12, 15 and 18 months of age during the intervention children’s achievements of the motor development milestones will be observed by the anthropometry team. We anticipate that this additional test will take approximately 10-15 minutes.

#### Location and duration of the study.

The study will be conducted in the Dandé Health District in Houet Province of southwestern Burkina Faso, West Africa. Dandé is located 56 kilometers from Bobo-Dioulasso. This area has been selected both because of high rates of nutritional stunting and because the IRSS,B has developed excellent rapport with local community leaders and residents.

In total, the duration of the study will be 33 months. The data collection will run for about 48 months. Data analysis and dissemination of results will occur over 24 months.

We anticipate that the duration of the study will be 4 years (including census, baseline data collection, intervention, follow-up, laboratory and data analysis). Subjects will be included in the intervention group will be included in the study for a period of approximately 3.5 years but will receive the intervention for only 9 months of that time. Recruitment is anticipated to begin in April 2010, with data collection lasting until the end of June 2012. Laboratory analyses and data entry are expected to be completed by December 2012, and data analysis will occur by June 2013.

